**Follow-up and ascertainment of outcome**

Individuals with previous arrhythmia (see below **Table 3** for ICD codes) before index date will be excluded. Follow-up will start at index date until incident diagnosis of arrhythmias, emigration, death, or December 31, 2019, whichever occurs first. Reference individuals or IBD-free full siblings will also be censored when receiving a diagnosis of IBD during follow-up. Individuals with an incident arrhythmia will be identified from the NPR, considering both primary and secondary diagnosis. The primary outcome is the incidence of overall arrhythmias. The secondary outcomes are the incidences of atrial fibrillation/flutter, bradyarrhythmias, other supraventricular arrhythmias, and ventricular arrhythmias/cardiac arrest. If one individual is diagnosed with more than one of the secondary outcomes, this individual will contribute to each outcome with the respective diagnosis date.

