**Covariates**

We will retrieve information on country of birth (available from 1947 onward, Nordic or others) from the Total Population Register [4] and educational attainment (available from 1990 onward; 4 groups: 0-9 y, 10-12 y, ≥13 y, and “missing”, a proxy for socioeconomic status) from the Swedish Longitudinal Integrated Database for Health Insurance and Labour Market Studies [6]. As a proxy for regular healthcare seeking behavior, number of healthcare visits will be retrieved from the NPR (4 groups: 0, 1, 2-3, and ≥4,) which is defined as the number of specialized (non-primary care) outpatient visits or hospitalizations between 2 years and 6 months before index date. Data on cardiovascular related comorbidities preceding index date will be collected from the NPR, including ischemic heart disease, heart failure, stroke, hypertension, diabetes, obesity dyslipidemia, chronic kidney disease, and chronic obstructive pulmonary disease (COPD, only if patient diagnosed ≥40 year) (see below **Table 4** for ICD codes). Information regarding use of the cardiovascular related medications preceding index date will be collected from the Prescribed Drug Register [7] (data available from July 2005 onward): aspirin, non-aspirin anti-platelet medications, statins, non-statin lipid lowering medications, anticoagulation medications, antidiabetic medications, and antihypertensive agents (see below **Table 5** for the Anatomical Therapeutic Chemical codes).

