**Subgroup and sensitivity analyses**

We will calculate the risk of overall arrhythmia by sex, age at index date (<18, 18-<40, 40-<60, and ≥60), calendar period at index date (1969-1989, 1990-1999, 2000-2009, and 2010-2019), educational attainment (0-9 y, 10-12 y, ≥13 y, and “missing”), and number of healthcare visits (0, 1, 2-3, and ≥4). We will also explore the associations by location for CD, by extent for UC according to the Montreal classification, and by occurrence of primary sclerosing cholangitis or other extraintestinal manifestations (see below **Table 2** for ICD codes) [3].

Several sensitivity analyses will be conducted. **First,** due to lack of detailed data on smoking, we will restrict the analysis to those without COPD (a proxy for heavy smoking) before index date. **Second,** we will restrict the analysis to individuals with data available on educational attainment. **Third,** given that the Prescribed Drug Register is available since July 2005, we will restrict the analysis to individuals with index date later than 1 January 2006 and apply the statistical models further adjusting for the above mentioned cardiovascular related medications. **Fourth,** we will repeat the main analysis after excluding individuals with incident arrhythmias recorded within 1 year or within 3 years of follow-up after index date. **Fifth,** we will compare patients with IBD with their IBD-free full siblings after conditioning on family identifier and adjusting for birth year, sex, county of residence, calendar year, and all above mentioned covariates.

Data analyses will be performed using SAS version 9.4 (SAS Institute Inc, Cary, NC), Stata (version 16.1; Stata Corp LP, College Station, TX), and R version 3.6.0. A two-sided *P* ≤ 0.05 will be considered statistically significant.

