|  | ICD-10: I20-25 |
| Heart failure | ICD-8: 428 |
|  | ICD-9: 428 |
|  | ICD-10: I42; I50 |
| Stroke | ICD-8: 431-434 |
|  | ICD-9: 431-434 |
|  | ICD-10: I61-64 |
| Hypertension | ICD-8: 400-404 |
|  | ICD-9: 401-405 |
|  | ICD-10: I10-I15 |
|  | Medication ATC codes: see antihypertensive medications in Table 5 |
| Obesity | ICD-8: 277 |
|  | ICD-9: 278A, 278B |
|  | ICD-10: E65-66 |
| Diabetes | ICD-8: 250 |
|  | ICD-9: 250 |
|  | ICD-10: E10-E14, O24 |
|  | Medication ATC codes: see antidiabetic medications in Table 5 |
| Dyslipidemia | ICD-8: 279 |
|  | ICD-9: 272 |
|  | ICD-10: E78 |
|  | Medication ATC codes: C10 |
| Chronic kidney disease | ICD-8: 585, 586, Y29,01 |
|  | ICD-9: 585, 586, 753B, V42A, V45B, V56 |
|  | ICD-10: N18, N19; N26; T824; Y841; Q61; Z49; Z992; Z940 |
| Chronic obstructive pulmonary disease (COPD)  (only if patient diagnosed ≥40 year) | ICD-8: 491, 492 |
|  | ICD-9: 491, 492, 496 |
|  | ICD-10: J41-J44 |

| **Table 5. Definitions of prescription medications** | |
| --- | --- |
| **Covariates** | **Definition** |
| Aspirin | B01AC06 |
| Non-aspirin anti-platelet medications | B01AC excluding aspirin (B01AC06) |
| Statins | C10AA |
| Non-statin lipid lowering medications | C10AB, C10AC, C10AD, C10AX01-14 |
| Anticoagulation medications | B01AA, B01AE, B01AF, B01AX |
| Antidiabetic medications | A10 |
| Antihypertensive medications | C02, C03AA-AB, C03BA, C03CA, C03DA, C03EA, C08CA, C08DA, C08DB, C09A, C09BA, C09BB, C09CA, C09DA, C09DB01 |

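### The drug list omits beta-blockers, antiarrhythmics and glycosides, and prior arrhythmia is screened by diagnosis codes alone, so some treated arrhythmia can be counted as incident, mainly early in follow-up

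*SAP*

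**What the plan says.** **Drugs.** The Covariates section names seven classes: "aspirin, non-aspirin anti-platelet medications, statins, non-statin lipid lowering medications, anticoagulation medications, antidiabetic medications, and antihypertensive agents". Beta-blockers, antiarrhythmics and glycosides are not among them. Table 5 gives the antihypertensive codes as "C02, C03AA-AB, C03BA, C03CA, C03DA, C03EA, C08CA, C08DA, C08DB, C09A, C09BA, C09BB, C09CA, C09DA, C09DB01" and the anticoagulant codes as "B01AA, B01AE, B01AF, B01AX". The dispensing register is described as having "data available from July 2005 onward".

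**Use of the drugs.** The third sensitivity analysis restricts to index dates after 1 January 2006 and will "apply the statistical models further adjusting for the above mentioned cardiovascular related medications". Table 4 also uses dispensing codes to help define hypertension, diabetes and dyslipidemia, and all three are covariates in model 2.

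**Prior and incident arrhythmia.** The follow-up section states: "Individuals with previous arrhythmia (see below Table 3 for ICD codes) before index date will be excluded". It then states: "Individuals with an incident arrhythmia will be identified from the NPR, considering both primary and secondary diagnosis". The Covariates section describes the visits counted from the National Patient Register (NPR) as specialised, non-primary care. No dispensing record is used to screen for earlier arrhythmia.

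**Related safeguards.** The fourth sensitivity analysis removes people whose arrhythmia was recorded within 1 or 3 years of index. Model 2 adjusts for the number of specialised visits between 2 years and 6 months before index.

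**The concern.** The missing classes bear on a recorded arrhythmia in two ways. They can alter the chance that one is recorded, and they can mark one that already exists. The list takes in the rate-slowing calcium blockers (C08DA, C08DB) but not beta-blockers, and the SAP gives no reason for the difference.

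The screening rule makes this matter. Someone whose arrhythmia is managed only outside specialist care has no Table 3 code and enters the cohort as arrhythmia-free. The first NPR contact that records it, even as a secondary diagnosis, is an incident event. IBD patients may have more such contacts after index because of their IBD. The visit covariate cannot correct for that, because its window closes 6 months before index.

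At stake are mainly the early results: the first part of the time-varying HR and the 1-year cumulative incidence difference, both of which the Statistical analyses section promises.

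**Working it through.** **Code check.** Searching every Table 5 code by prefix finds none beginning C07, C01A or C01B. C08DA, C08DB and four anticoagulant groups are present. The drug meaning of each prefix is that of the ATC classification the SAP uses; the omission by name can be read from the Covariates section alone.

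**Size.** The SAP gives no figure on this point, so there is nothing to reproduce and every input here is an assumption:
- p = 1% or 2% of each arm enters with a treated arrhythmia unknown to the NPR
- true rate in everyone else: r0 = 0.008 per year in references; r1 = 1.2 × 0.008 = 0.0096 in IBD
- these hidden cases are first coded at rate d per year: 10% in IBD versus 5% in references, or 20% versus 10%

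HR at index = [(1−p)·r1 + p·d1] / [(1−p)·r0 + p·d0].

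For p = 1%, 10% versus 5%: (0.99 × 0.0096 + 0.01 × 0.10) / (0.99 × 0.008 + 0.01 × 0.05) = 0.01050 / 0.00842 = 1.25.

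The hidden pool empties as cases are coded, so the average over follow-up is smaller. With S(t) = (1−p)·exp(−r·t) + p·exp(−d·t), the rate over an interval is the fall in S divided by the area under S. For the same scenario over 10 years: IBD 0.09694 / 9.503 = 0.01020; references 0.08005 / 9.593 = 0.00834; ratio 1.22.

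| p | coding, IBD vs reference | HR at index | 0–10 y | 0–20 y | years 3–10 |
|---|---|---|---|---|---|
| 1% | 10% vs 5% | 1.25 | 1.22 | 1.21 | 1.215 |
| 1% | 20% vs 10% | 1.29 | 1.22 | 1.20 | 1.198 |
| 2% | 10% vs 5% | 1.29 | 1.24 | 1.22 | 1.230 |
| 2% | 20% vs 10% | 1.36 | 1.23 | 1.20 | 1.196 |

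The last column approximates the planned 3-year lag by starting follow-up at year 3.

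**Equal coding.** With p = 2% and 10% in both arms, the HR at index is (0.98 × 0.0096 + 0.002) / (0.98 × 0.008 + 0.002) = 0.01141 / 0.00984 = 1.16, below the true 1.20. With p = 1% and 5% in both arms it is 0.01000 / 0.00842 = 1.19.

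**One-year cumulative incidence difference.** Without hidden cases it is about 1.6 per 1,000. For p = 2% and 20% versus 10%:
- IBD: 1 − (0.98·e^−0.0096 + 0.02·e^−0.2) = 0.01299
- references: 1 − (0.98·e^−0.008 + 0.02·e^−0.1) = 0.00971
- difference: 3.3 per 1,000

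For p = 1% and 10% versus 5% the difference is 2.0 per 1,000.

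**Milder inputs.** With p = 0.25% to 1%, a reference rate of 6 per 1,000 person-years, a true ratio of 1.0 and coding of 20% versus 10%, the 10-year ratio is 1.01 to 1.04. From year 3 it is 1.00 to 1.01.

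**The case against.** The case against is substantial, and most of it stands.

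- **The bias is modest on average.** A reader might take 1.25 to 1.36 as the HR the study would report. It is not: those values apply only at index, before any hidden case has been coded. The objective is long-term risk, and over 10 to 20 years the excess is 0.04 or less.
- **The lag analysis works fairly well.** From year 3 the ratio is within 0.03 of the truth in all four scenarios. It works less well when coding is slow. With p = 2%, 8 per 1,000 and a true ratio of 1.0, coding of 10% versus 5% gives 1.061 over 10 years and still 1.046 from year 3; 20% versus 10% falls from 1.057 to 1.019.
- **The direction is conditional.** The documents do not show that hidden arrhythmia is coded faster in IBD. With equal coding the bias runs slightly towards the null.
- **Background treatment is not ignored elsewhere.** One might infer that the third sensitivity analysis is the only place it enters. Table 4 shows otherwise, through the dispensing-based definitions in model 2. A non-prespecified analysis also excludes people with cardiovascular-related comorbidities.
- **Table 5 is not blind to treated arrhythmia.** Anticoagulants and C08DA/C08DB will mark some of it, though only as covariates.
- **Nothing is contradictory.** Table 5 agrees with the Covariates section, and using the same codes for prior and incident disease is coherent.

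What remains is that antiarrhythmic and glycoside users are neither flagged nor excluded, although the register that would identify them is already a data source.

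**Conclusion.** The point holds as a cheap improvement to one sensitivity analysis. The two facts are certain from the text: the three drug classes are absent, and prior arrhythmia is screened by diagnosis codes only. That hidden cases exist follows from the SAP's description of NPR visits as non-primary care; their number is unknown.

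Inflation of the HR depends on faster coding in IBD after index. Under the assumptions above, a true 1.20 becomes 1.25 to 1.36 at index, about 1.22 to 1.24 over 10 years and about 1.20 to 1.23 after the 3-year lag. The early time-varying HR and the 1-year difference are the most exposed.

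A reader might conclude that the primary result is invalid. The documents do not support that: the average distortion is small on these inputs, and planned analyses already absorb part of it.

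**What to change.** In the third sensitivity analysis (index after 1 January 2006):

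1. Exclude anyone with a C01B or C01AA dispensing before index as a presumed prevalent case, by the same rule in patients, references and siblings. Report the number excluded by arm; that count is itself evidence on whether the problem matters.
2. Add C07 to Table 5 as a separate covariate, leaving the Table 4 hypertension definition unchanged. Report the model with and without it, because beta-blockers have several indications.
3. State as limitations that prevalent arrhythmia treated only with a beta-blocker is not removed, and that index dates before the drug register starts cannot be screened this way. For index dates early in 2006 the look-back is only about six months.

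List the additions under the SAP's existing heading for non-prespecified analyses.

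**Cost:** three ATC groups from a register already in use, one rerun, and the loss of a few people taking these drugs for other reasons. The primary analysis is unchanged.
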